## 3.2 Exclusion Criteria

- 3.2.1 History of another malignancy.

Exception: Patients who have been disease-free for 3 years, or patients with a history of completely resected non-melanoma skin cancer and/or patients with indolent secondary malignancies, are eligible. Consult the CTEP Medical Monitor if unsure whether second malignancies meet the requirements specified above.

- 3.2.2 History of interstitial lung disease or pneumonitis.

- 3.2.3 Any major surgery, extensive radiotherapy, chemotherapy with delayed toxicity, biologic therapy, or immunotherapy within 28 days prior to enrollment and/or daily or weekly chemotherapy without the potential for delayed toxicity within 14 days prior to enrollment.

- 3.2.4 Use of other investigational drugs within 28 days (or five half-lives, whichever is shorter; with a minimum of 14 days from the last dose) preceding the first dose of trametinib and during the study. Patients previously treated with RAF and/or MEK inhibitors are excluded from the study. Multikinase antiangiogenic tyrosine kinase inhibitors such as regorafenib, sofarenib, sunitinib, etc. whose primary mechanism of action is not RAF inhibition, are allowed. If there are any questions, please contact study's Principal Investigator."
- 3.2.5 Symptomatic or untreated leptomeningeal or brain metastases or spinal cord compression.
- 3.2.6 Have a known immediate or delayed hypersensitivity reaction or idiosyncrasy to drugs chemically related to trametinib or excipients or to dimethyl sulfoxide (DMSO).
- 3.2.7 Current use of a prohibited medication. The following medications or non-drug therapies are prohibited:
- Other anti-cancer therapy while on study treatment. (Note: megestrol [Megace] if used as an appetite stimulant is allowed).
  - Concurrent treatment with bisphosphonates is permitted; however, treatment must be initiated prior to the first dose of study therapy. Prophylactic use of bisphosphonates in patients without bone disease is not permitted, except for the treatment of osteoporosis.
  - Because the composition, PK, and metabolism of many herbal supplements are unknown, the concurrent use of all herbal supplements is prohibited during the study (including, but not limited to, St. John's wort, kava, ephedra [ma huang], ginkgo biloba, dehydroepiandrosterone [DHEA], yohimbe, saw palmetto, or ginseng).
- 3.2.8 History or current evidence/risk of retinal vein occlusion (RVO).
- 3.2.9 History or evidence of cardiovascular risk including any of the following:
- LVEF<LLN.
  - A QT interval corrected for heart rate using the Bazett's formula  $QTcB \geq 480$  msec.
  - History or evidence of current clinically significant uncontrolled arrhythmias (exception: patients with controlled atrial fibrillation for >30 days prior to randomization are eligible).
  - History of acute coronary syndromes (including myocardial infarction and unstable angina), coronary angioplasty, or stenting within 6 months prior to randomization.
  - History or evidence of current  $\geq$  Class II congestive heart failure as defined by the New York Heart Association (NYHA) functional classification system
  - Treatment-refractory hypertension defined as a blood pressure of systolic >140 mmHg and/or diastolic >90 mmHg which cannot be controlled by anti-hypertensive therapy.
  - Patients with intra-cardiac defibrillators

- Known cardiac metastases.

- 3.2.10 Active Hepatitis B Virus (HBV), or Hepatitis C Virus (HCV) infection (patients with chronic or cleared HBV and HCV infection are eligible). Patients with known HIV infection are eligible if not on antiviral agents and CD4 counts are adequate ( $\geq 500$ ).
- 3.2.11 Uncontrolled inter-current illness including, but not limited to, ongoing or active infection, symptomatic congestive heart failure, unstable angina pectoris, cardiac arrhythmia, or psychiatric illness/social situations that would limit compliance with study requirements.
- 3.2.12 Animal reproductive studies have not been conducted with trametinib. Therefore, the study drug must not be administered to pregnant women or nursing mothers. Women of childbearing potential should be advised to avoid pregnancy and use effective methods of contraception. Men with a female partner of childbearing potential must have either had a prior vasectomy or agree to use effective contraception. If a female patient or a female partner of a patient becomes pregnant while the patient receives trametinib, the potential hazard to the fetus should be explained to the patient and partner (as applicable).
- 3.2.13 HIV-positive patients on combination antiretroviral therapy are ineligible because of the potential for pharmacokinetic interactions. In addition, these patients are at increased risk of lethal infections when treated with marrow-suppressive therapy. Appropriate studies will be undertaken in patients receiving combination antiretroviral therapy when indicated.
- 3.2.14 Any condition or medical problem in addition to the underlying malignancy and organ dysfunction which the investigator feels would pose unacceptable risk.

### 3.3 Inclusion of Women and Minorities

Both men and women of all races and ethnic groups are eligible for this trial. This study is designed to include minorities as appropriate. However, the trial is not designed to measure differences in intervention effects.

## 4. REGISTRATION PROCEDURES

### 4.1 Investigator and Research Associate Registration with CTEP

#### 4.1.1 CTEP Registration Procedures

Food and Drug Administration (FDA) regulations and National Cancer Institute (NCI) policy require all investigators participating in any NCI-sponsored clinical trial to register and to renew their registration annually.

Registration requires the submission of:

- a completed *Statement of Investigator Form* (FDA Form 1572) with an original signature
- a current Curriculum Vitae (CV)
- a completed and signed *Supplemental Investigator Data Form* (IDF)
- a completed *Financial Disclosure Form* (FDF) with an original signature

Fillable PDF forms and additional information can be found on the CTEP website at [http://ctep.cancer.gov/investigatorResources/investigator\\_registration.htm](http://ctep.cancer.gov/investigatorResources/investigator_registration.htm). For questions, please contact the *CTEP Investigator Registration Help Desk* by email at [[contact]](mailto:[contact]).

#### 4.1.2 CTEP Associate Registration Procedures / CTEP-IAM Account

The Cancer Therapy Evaluation Program (CTEP) Identity and Access Management (IAM) application is a web-based application intended for use by both Investigators (i.e., all physicians involved in the conduct of NCI-sponsored clinical trials) and Associates (i.e., all staff involved in the conduct of NCI-sponsored clinical trials).

Associates will use the CTEP-IAM application to register (both initial registration and annual re-registration) with CTEP and to obtain a user account.

Investigators will use the CTEP-IAM application to obtain a user account only. (See CTEP Investigator Registration Procedures above for information on registering with CTEP as an Investigator, which must be completed before a CTEP-IAM account can be requested.)

An active CTEP-IAM user account is needed to access all CTEP and CTSU (Cancer Trials Support Unit) websites and applications, and is critical to the conduct of this study, including document access, patient enrollment, and clinical data submission.

Additional information can be found on the CTEP website at [http://ctep.cancer.gov/branches/pmb/associate\\_registration.htm](http://ctep.cancer.gov/branches/pmb/associate_registration.htm). For questions, please contact the *CTEP Associate Registration Help Desk* by email at [[contact]](mailto:[contact]).

## 4.2 Site Registration

This study is supported by the NCI Cancer Trials Support Unit (CTSU).

Each investigator or group of investigators at a clinical site must obtain IRB approval for this protocol and submit IRB approval and supporting documentation to the CTSU Regulatory Office before they can be approved to enroll patients. Assignment of site registration status in the CTSU Regulatory Support System (RSS) uses extensive data to make a determination of whether a site has fulfilled all regulatory criteria including but not limited to: an active Federal Wide Assurance (FWA) number, an active roster affiliation with the Lead Network or a participating organization, a valid IRB approval, and compliance with all protocol specific requirements.

### 4.2.1 Downloading Regulatory Documents

Site registration forms may be downloaded from the 9591 protocol page located on the CTSU Web site. Permission to view and download this protocol is restricted and is based on person and site roster data housed in the CTSU RSS. To participate, Investigators and Associates must be associated with the Corresponding or Participating protocol organization in the RSS.

- Go to <https://www.ctsuo.org> and log in using your CTEP IAM username and password
- Click on the Protocols tab in the upper left of your screen
- Either enter the protocol # in the search field at the top of the protocol tree, or
- Click on the By Lead Organization folder to expand, followed by LAO-11030, and protocol # 9591
- Click on LPO Documents sub-tab, select the Site Registration documents link, and download and complete the forms provided.

### 4.2.2 Submitting Regulatory Documents

Both U.S. and Canadian sites must submit their Model Informed Consent to the Study Coordinator at the University Health Network Princess Margaret Cancer Center (listed on protocol face page) for **pre**-approval prior to submitting to their local IRB/REB.

U.S. sites will submit completed forms along with a copy of the IRB Approval and Model Informed Consent to the CTSU Regulatory Office, where they will be entered and tracked in the CTSU RSS.

Regulatory Submission Portal: [www.ctsuo.org](http://www.ctsuo.org) (members' area) → Regulatory Tab

→Regulatory Submission

When applicable, original documents should be mailed to:

CTSU Regulatory Office  
[name]  
[name]

Institutions with patients waiting that are unable to use the Portal should alert the CTSU Regulatory Office immediately at [name] in order to receive further instruction and support.

Canadian sites will submit their REB initial approval along with the Model Informed Consent and all future amendment approvals to the University Health Network Princess Margaret Cancer Center for review. The University Health Network Princess Margaret Cancer Center will then send notification of document approval to the CTSU Regulatory Office for tracking and compliance in RSS.

Requirements for 9591 Site Registration:

- CTSU Transmittal Sheet (optional)
- IRB approval (For sites not participating via the NCI CIRB; local IRB documentation, an IRB-signed CTSU IRB Certification Form, Protocol of Human Subjects Assurance Identification/IRB Certification/Declaration of Exemption Form, or combination is accepted)

#### 4.2.3 Checking Site Registration Status

You can verify your site registration status on the members' section of the CTSU website.

- Go to <https://www.ctsuo.org> and log in to the members' area using your CTEP-IAM username and password
- Click on the Regulatory tab at the top of your screen
- Click on the Site Registration tab
- Enter your 5-character CTEP Institution Code and click on Go

Note: The status given only reflects compliance with IRB documentation and institutional compliance with protocol-specific requirements as outlined by the Lead Network. It does not reflect compliance with protocol requirements for individuals participating on the protocol or the enrolling investigator's status with the NCI or their affiliated networks.

### 4.3 Patient Registration

#### 4.3.1 OPEN / IWRS

Patient enrollment will be facilitated using the Oncology Patient Enrollment Network (OPEN). OPEN is a web-based registration system available to users on a 24/7 basis. It is integrated with the CTSU Enterprise System for regulatory and roster data interchange and with the Theradex Interactive Web Response System (IWRS) for retrieval of patient registration/randomization assignment. Patient enrollment data entered by Registrars in OPEN / IWRS will automatically transfer to the NCI's clinical data management system, Medidata Rave.

For trials with slot reservation requirements, OPEN will connect to IWRS at enrollment initiation to check slot availability. Registration staff should ensure that a slot is available and secured for the patient before completing an enrollment.

The OPEN system will provide the site with a printable confirmation of registration and treatment information. Please print this confirmation for your records.

#### 4.3.2 OPEN/IWRS User Requirements

OPEN/IWRS users must meet the following requirements:

- Have a valid CTEP-IAM account (*i.e.*, CTEP username and password).
- To enroll patients or request slot reservations: Be on an ETCTN Corresponding or Participating Organization roster with the role of Registrar.
- To approve slot reservations or access cohort management: Be identified to Theradex as the "Client Admin" for the study.
- Have regulatory approval for the conduct of the study at their site.

Prior to accessing OPEN/IWRS, site staff should verify the following:

- All eligibility criteria have been met within the protocol stated timeframes.
- If applicable, all patients have signed an appropriate consent form and HIPAA authorization form.

#### 4.4 General Guidelines

Following registration, patients should begin protocol treatment within 5 days. Issues that would cause treatment delays should be discussed with the Principal Investigator. If a patient does not receive protocol therapy following registration, the patient's registration on the study may be canceled. The Study Coordinator should be notified of cancellations as soon as possible. A record of patients who fail to meet entry criteria (*i.e.* screen failures) will be maintained.

### 5. TREATMENT PLAN

#### 5.1 Stratification by Hepatic Function

##### 5.1.1 Study Definition of Hepatic Dysfunction Group

Patients entering this study will be stratified into 4 groups or cohort according to their hepatic function as outline in the following table (Table 6):

**Table 6:** Defining criteria for the four cohorts based on hepatic function.

| Group | Hepatic Function             | Hepatic Function                                                                              |
|-------|------------------------------|-----------------------------------------------------------------------------------------------|
| A     | Normal hepatic function      | Bilirubin $\leq$ ULN
AST $\leq$ ULN                                                        |
| B     | Mild hepatic dysfunction     | B1: bilirubin $\leq$ ULN and AST $>$ ULN
B2: ULN $<$ bilirubin $\leq$ 1.5x ULN and any AST |
| C     | Moderate hepatic dysfunction | 1.5x ULN $<$ bilirubin $\leq$ 3x ULN and any AST                                              |
| D     | Severe hepatic dysfunction   | 3x ULN $<$ bilirubin $\leq$ 10x ULN and any AST                                               |

ULN= upper limit of normal

- Patients must fulfill both total bilirubin and SGOT/AST criteria to be included in a group. However, if a patient's total bilirubin level and SGOT/AST level indicate different groups, the patient may be enrolled in the indicated group with the greatest degree of liver dysfunction.
- No distinction will be made between liver dysfunction due to metastases and liver dysfunction due to other causes.
- All liver function tests must be completed within 24 hours prior to the start of treatment.
- Group B (mild): For the purposes of this study, the "mild" liver dysfunction may be defined according to either of two criteria (B1 and B2), so that patients in Group B may come from either of these groups. Patients in Groups B1 and B2 are thus considered to have comparable liver dysfunction and will be combined for dose level allocation and all analyses.
- Patients whose degree of hepatic dysfunction changes (becomes worse or better) between registration and initiation of protocol therapy may be re-assigned to a different dysfunction

group and dose level. This change should be discussed with the Principal Investigator. The Central Office Study Coordinator must document reassignments with notification to Theradex.

- Group A (normal): Patients in group A are included in this study as control subjects and will be followed for toxicity; however, the definitions of DLT in section 5.3 will not apply and a recommended dose will not be defined in these patients because the MTD has already been defined in such patients.

#### 5.1.2 Child-Pugh Classification (CPC) of hepatic dysfunction

Each patient's CPC score (for liver dysfunction cohorts: B, C, and D) should be calculated at baseline and prior each treatment cycle. See [Appendix B](#) for instructions on CPC calculation.

### 5.2 Trametinib Dimethyl Sulfoxide (GSK1120212B, MEKINIST™) Administration

Treatment will be administered orally on an outpatient basis. Reported adverse events and potential risks are described in Section 7. Appropriate dose modifications are described in Section 6. No investigational or commercial agents or therapies other than those described below may be administered with the intent to treat the patient's malignancy.

Patients will receive trametinib taken orally once a day continuously of a 28-day cycle (Table 7).

**Table 7:** Dosing details for trametinib.

| Regimen Description |                                                              |                                  |       |          |                   |
|---------------------|--------------------------------------------------------------|----------------------------------|-------|----------|-------------------|
| Agent               | Premedications; Precautions                                  | Dose                             | Route | Schedule | Cycle Length      |
| Trametinib          | Not required; Empty stomach (1hr before or 2hr after a meal) | To be assigned by central office | Oral  | Daily    | 28 days (4 weeks) |

To allow for liver function testing within 24 hours before drug administration and maximum PK sampling within a standard working week, the first dose of trametinib should be administered on a Tuesday or Wednesday. However, for those institutions with resources able to obtain PKs on weekends, treatment may be started on other days.

Dose escalation will follow the schedule summarized in the table below (Table 8). All 4 liver dysfunction cohorts (A, B, C, D) may be open concomitantly.

NOTE: The patient will be requested to maintain a medication diary of each dose of medication (Appendix F). The medication diary will be returned to clinic staff at the end of each course.

**Table 8:** Dose escalation schema for each cohort as defined by hepatic function.

|                       | Group A                     | Group B                      | Group C                          | Group D                        |
|-----------------------|------------------------------------|-------------------------------------|-----------------------------------------|---------------------------------------|
|                       | Normal
hepatic function | Mild
hepatic dysfunction | Moderate
hepatic dysfunction | Severe
Hepatic dysfunction |
| Dose
Level | mg                                 | mg                                  | mg                                      | mg                                    |
| Level - 2             | -                                  | 1                                   | 0.5                                     | -                                     |
| Level - 1             | -                                  | 1.5                                 | 1                                       | 0.5                                   |
| Level 1               | 2                                  | 2                                   | 1.5                                     | 1                                     |
| Level +1              | no escalation                      | no escalation                       | 2                                       | 1.5                                   |
| Level +2              | no escalation                      | no escalation                       | no escalation                           | 2                                     |

### 5.2.1 Trametinib

The effect of food on trametinib absorption is unknown. The current recommendation is to administer trametinib on an empty stomach, 1 hour before or 2 hours after a meal; the recommendation to administer trametinib fasting may change based on emerging data.

## 5.3 Definition of Dose-Limiting Toxicity

Toxicities will be graded according to the NCI Common Toxicity Criteria for Adverse Events version 4.0.0 (CTCAE v4.0.0). Dose-limiting toxicity (DLT) will be a toxicity that occurs during cycle 1 (first 28 days) and is felt to be possibly, probably or definitely related to the study drug.

The definition of DLT (Sections 5.3.1 and 5.3.2) and approaches for dose modification (Section 6) are provided in the protocol documents.

### 5.3.1 Hematologic Toxicity:

- Grade 3 or 4 neutropenia complicated by fever  $\geq 38.5^{\circ}\text{C}$  or infection
  - Grade 4 neutropenia of at least 7 days duration
  - Grade 3 thrombocytopenia complicated by hemorrhage
  - Grade 4 thrombocytopenia.
- Note:* Grade 4 lymphopenia, anemia, or leucopenia without neutropenia will NOT constitute a DLT. Grade 4 neutropenia that is disease related will not count as DLT

### 5.3.2 Non-Hematologic toxicity:

- Allergic reaction/hypersensitivity will not be considered dose-limiting
- Alopecia will not be considered dose limiting
- Any Grade 4 non-hematologic toxicity
- Grade 3 non-hematologic toxicity (except nausea, vomiting or diarrhea that can be controlled by appropriate medical intervention or prophylaxis and that resolves to Grade 1 within 48 hours with medical intervention or electrolyte toxicities unable to

be corrected to  $\leq$  Grade 1 or baseline within 48 hours) excluding specific toxicities (\* see below)

- Treatment-related toxicities that result in failure to receive  $\geq 75\%$  of trametinib doses in cycle 1 despite maximal supportive care measures
- Delays in starting cycle 2 by  $\geq 2$  weeks due to treatment-related toxicity will constitute a DLT

\* **Liver toxicity:** Worsening liver function, as defined by a rise in serum bilirubin, not related to tumor progression or stent occlusion will constitute a DLT if:

- For patients in the Hepatic Dysfunction cohorts (B, C, D):

Mild group (B): progresses into severe dysfunction range for 1 week or longer.

Moderate group (C): bilirubin increases from baseline  $\geq 3$  fold for 1 week or longer.

Severe group (D): bilirubin increases from baseline  $\geq 2$  fold for 1 week or longer.

*Note:* Patients requiring stent placement during study treatment will be allowed to continue study treatment after stent placement and a period of stabilization of clinical status and liver function tests. Two measurements at least 2 days apart will be accepted as evidence of stable hepatic function.

\* **Cardiac related toxicity:** symptomatic cardiac failure;  $\geq$  grade 3 LV systolic dysfunction reduction in LVEF  $\geq 10$  points from baseline and below the institution's lower limit of normal, without improvement within 2 weeks; QTc > 500 msec; other  $\geq$  grade 3 cardiac disorders.

Management and dose modifications associated with the above adverse events are outlined in Section 6.

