## Dose Escalation Schema

Dose escalation will proceed within each cohort according to the following schema (Table 9).

**Table 9:** Dose escalation schema for each cohort as defined by hepatic function.

|            | Group A                 | Group B                  | Group C                      | Group D                    |
|------------|-------------------------|--------------------------|------------------------------|----------------------------|
|            | Normal hepatic function | Mild hepatic dysfunction | Moderate hepatic dysfunction | Severe hepatic dysfunction |
| Dose Level | mg                      | mg                       | mg                           | mg                         |
| Level - 2  | -                       | 1                        | 0.5                          | -                          |
| Level - 1  | -                       | 1.5                      | 1                            | 0.5                        |
| Level 1    | 2                       | 2                        | 1.5                          | 1                          |
| Level +1   | no escalation           | no escalation            | 2                            | 1.5                        |
| Level +2   | no escalation           | no escalation            | no escalation                | 2                          |

Dose-limiting toxicity (DLT) is defined above (Sections 5.3.1. and 5.3.2).

The patient's starting dose will be assigned by the Central Office Study Coordinator at the time of registration. The patients' hepatic dysfunction group may be altered after registration if hepatic function tests performed within 24 hours of commencing trametinib have changed from registration results as described in section 5.1.1. The dose may be reduced for individual patients in subsequent cycles depending on toxicity as outlined in section 6.

Normal, mild, moderate and severe liver dysfunction cohorts may be open concurrently.

The initial cohorts of patients will begin on dose level 1 based on their level of hepatic dysfunction. Liver function tests (AST and total bilirubin) should be repeated within 24 hours prior to starting treatment on study to determine hepatic dysfunction cohort.

Escalation is planned as the standard "3+3" schema, for each hepatic dysfunction cohort (Cohorts B, C and D), with the exception of the normal hepatic function cohort (Cohort A) (Table 10).

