**Table 10:** Dose escalation and cohort expansion rules using the standard 3+3 design.

| Number of Patients with DLT at a Given Dose Level                         | Escalation Decision Rule                                                                                                                                                                                                                                                                                                                                                                                                                                        |
|---------------------------------------------------------------------------|-----------------------------------------------------------------------------------------------------------------------------------------------------------------------------------------------------------------------------------------------------------------------------------------------------------------------------------------------------------------------------------------------------------------------------------------------------------------|
| 0 out of 3                                                                | Enter 3 patients at the next dose level.                                                                                                                                                                                                                                                                                                                                                                                                                        |
| ≥ 2                                                                       | Dose escalation will be stopped. This dose level will be declared the maximally administrated dose (highest dose administrated). Three (3) additional patients will be entered at the next lowest dose level if only 3 patients were treated previously at that dose.                                                                                                                                                                                           |

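### Section 5.3.2 contradicts itself on Grade 3 electrolyte events: one exception clause exempts gut toxicity that resolves within 48 hours but electrolyte toxicity that does not

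*Protocol*

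**What the plan says.** Protocol Section 5.3.2 lists the non-hematologic DLT criteria. The bullet at issue opens "Grade 3 non-hematologic toxicity (except nausea, vomiting or diarrhea that can be controlled by appropriate medical intervention or prophylaxis", runs on "and that resolves to Grade 1 within 48 hours with medical intervention or electrolyte toxicities unable to" be corrected, and closes with "Grade 1 or baseline within 48 hours) excluding specific toxicities". The parenthesis that begins with the word *except* ends only after the electrolyte clause. The starred specific toxicities that follow cover the liver and the heart, not electrolytes.

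Three other bullets in the same list can still make an electrolyte event a DLT:

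- "Any Grade 4 non-hematologic toxicity";
- "Treatment-related toxicities that result in failure to receive" at least 75% of the cycle 1 doses;
- a start of cycle 2 postponed by two or more "weeks due to treatment-related toxicity will constitute a DLT".

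The Dose Escalation Schema adds no definition of its own: "Dose-limiting toxicity (DLT) is defined above (Sections 5.3.1. and 5.3.2". Table 10 then acts on the count. With no DLT in three patients the instruction is "Enter 3 patients at the next dose level"; with one in three, at least three more patients enter at the same level; with two or more, escalation stops. Section 13.3 takes as the recommended dose the highest level with at most 1 of 6 patients having a DLT.

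**The concern.** The two halves of the parenthesis use opposite tests. The gut events are excepted because they are brought under control within 48 hours. The electrolyte events are excepted because they are not. A reader who follows the words and a reader who follows the sense of the first half will disagree on every Grade 3 electrolyte event that this bullet decides.

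The DLT count in Groups B, C and D is taken from three to six patients per dose level, and MTD and DLT are primary endpoints. The situation is foreseeable. Section 7.1 lists hyponatremia and hypomagnesemia as possibly related to trametinib, in the column for 20% or less, and the Study Calendar has chemistry that includes sodium, potassium, calcium, magnesium and phosphate on days 8, 15 and 22 of cycle 1. Several sites will classify such events, and no other section tells them which way.

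**Working it through.** The protocol has no figure of its own here to reproduce. The check has three parts.

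**1. What each reading gives.** The event is a Grade 3 electrolyte toxicity in cycle 1, at least possibly drug-related, with no other criterion met.

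| Reading of the clause | Corrected within 48 h | Not corrected within 48 h |
|---|---|---|
| Literal: inside the exception | DLT (general Grade 3 rule) | Not a DLT under this bullet |
| Parallel to the gut clause | Not a DLT | DLT |
| Clause treated as a separate DLT criterion outside the parenthesis | DLT (general Grade 3 rule) | DLT |

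The literal and parallel readings disagree in both columns. No two readings agree in both.

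**2. How much the other bullets catch.** A cycle has 28 daily doses, and 0.75 × 28 = 21, so a patient may miss up to 28 − 21 = 7 and still meet the 75% requirement. Table 12 (Section 6.1.1) interrupts treatment for a related Grade 3 toxicity until it returns to Grade 1 or baseline. If dosing stops on day d and the event persists to day 28, the missed doses number 29 − d. That reaches 8 when d is 21 or earlier, so such an event becomes a DLT through the missed-dose bullet. What remains outside is:

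- an event uncorrected at 48 hours that costs no more than 7 doses;
- an event stopping dosing after day 21 that does not delay cycle 2 by two weeks.

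For corrected events there is no counterpart: nothing in the list takes back a DLT assigned under the general Grade 3 rule.

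Section 13.1 adds a complication. A patient who receives other than the prescribed dose and has no DLT is inevaluable and is replaced, except a Group D patient who completes the day 16 PK schedule. A patient interrupted for an electrolyte event that the literal text exempts might therefore leave the count altogether.

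**3. What one event does.** Under Table 10, one reclassified patient changes 0/3 (next level) to 1/3 (add patients), and under Section 13.3 it changes 1/6 (acceptable) to 2/6 (not acceptable).

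For scale, let p be the probability that a patient has a counted DLT. The probability that a level clears the 3+3 rule is

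P(clear) = (1 − p)³ + 3p(1 − p)² × (1 − p)³.

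At p = 0.20: 0.512 + 0.384 × 0.512 = 0.709. At p = 0.25: 0.422 + 0.422 × 0.422 = 0.600.

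The rates below are assumptions. The base rate is the proportion with any other DLT. The added rate is the proportion whose only candidate DLT is a Grade 3 electrolyte event of the kind in dispute, not caught by another bullet.

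| Base rate | Not counted | Counted, 2% added | Counted, 5% added | Counted, 10% added |
|---|---|---|---|---|
| 10% | 0.906 | 0.871 | 0.814 | 0.709 |
| 20% | 0.709 | 0.665 | 0.600 | 0.494 |
| 30% | 0.494 | 0.454 | 0.396 | 0.309 |

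The difference is 3.5 to 4.4 points at 2%, 9 to 11 points at 5%, and 18.5 to 21.4 points at 10%. The same arithmetic applies to uncorrected events left out and to corrected events counted; only the direction relative to the other reading changes.

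**The case against.** A reader might infer that the definition hides serious, persistent electrolyte toxicity in general, so that a cohort with a true 2/6 is reported as 1/6. The documents do not support that. Grade 4 events count regardless, and the interruption rule with the 75% requirement catches most events that begin by day 21 and stay uncorrected. Nor can any count be called true while the protocol does not settle which rule applies. The clause may be a misplaced parenthesis as easily as a reversed condition, and a site that treats it as a separate criterion would count uncorrected events. These objections stand and narrow the point.

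It is also too much to say that DLTs alone drive the dose. Doses are capped by those in less impaired groups (Dose Escalation Schema and Section 13.1), PK data are anticipated before escalation (Section 9.1), and the Protocol Principal Investigator signs off dose decisions (Section 12.1). None of these says whether a given electrolyte event is a DLT, so they do not remove the contradiction.

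Finally, the events may be rare. Section 7.1 lists hypokalemia, hyperkalemia, hypocalcemia and hyperphosphatemia among events with insufficient evidence of a causal link, and a DLT requires at least possible attribution within the first 28 days. The frequency is indeed unknown, and the table above rests on assumed rates.

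**Conclusion.** The clause is wrong as written, in the sense that it applies opposite tests to two exceptions in one sentence and no other section repairs it. The reach is limited to drug-related Grade 3 electrolyte events in cycle 1. For uncorrected events, the gap is what escapes the three other bullets; for corrected events, nothing in the protocol offsets the literal result. Within that reach, a single event is enough to change a cohort's decision. Because the recommended dose in one group limits the dose in more impaired groups, the effect could carry over. The size in practice depends on an event rate that the protocol does not give; the 2% to 10% range is illustrative. The conclusion rests on the printed text alone, not on a view of which electrolyte rule is clinically right.

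**What to change.** The sponsor should reconcile the two halves of the parenthesis so that Section 5.3.2 says explicitly, for a Grade 3 electrolyte event corrected within 48 hours and for one not corrected, whether each is a DLT. Which rule applies is for the sponsor to decide. Moving the electrolyte phrase to a bullet of its own would not be enough: it settles the uncorrected events but leaves corrected ones under the general Grade 3 rule without saying whether that is meant.

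The cycle 1 Grade 3 electrolyte events already recorded in Groups B, C and D should then be re-checked against the reconciled text. That check should include patients replaced as inevaluable, and any dose decision that turned on such an event should be reviewed. The cost is a one-sentence amendment and a short review of existing records.
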